### **Independent variables:**

*feedback control variables (T1-To / T2-To, at 1.4 km/h):*

- $\Delta R^2$  (feedback model relating foot placement to centre of mass movement)
- $\Delta$  RMS error (feedback model relating foot placement to centre of mass movement)
- $\Delta$  Position gain (feedback model relating foot placement to centre of mass movement)
- $\Delta$  Velocity gain (feedback model relating foot placement to centre of mass movement)

*neural correlates (T1-To / T2-To, at 1.4 km/h):*

- $\Delta$  beta power during walking at preferred speed
- $\Delta$  EEG-EMG coherence during walking at preferred speed

Associations between feedback control variables and neurological correlates

### **Dependent variables:**

*feedback control variables (T1-To / T2-To, at 1.4 km/h):*

- $\Delta R^2$  (feedback model relating foot placement to centre of mass movement)
- $\Delta$  RMS error (feedback model relating foot placement to centre of mass movement)
- $\Delta$  Position gain (feedback model relating foot placement to centre of mass movement)
- $\Delta$  Velocity gain (feedback model relating foot placement to centre of mass movement)

### **Independent variables:**

*neural correlates (T1-To / T2-To, at 1.4 km/h):*

- $\Delta$  beta power during walking at preferred speed
- $\Delta$  EEG-EMG coherence during walking at preferred speed

### **Analysis technique:**

We will correlate changes in primary outcomes (e.g., walking speed) with changes in behavioural (foot placement coordination) and neural (EEG beta band power, cortico-muscular coherence) outcomes. Multilevel models will be used, to account for data collected at different sites. For outcomes T2-To, potential predictors of clinical outcomes will include independent variables with a time lag (T1-To) and without time lag (T2-To).

## **ix. Daily life Mobility (3c)**

During the home assessment (To and T1), participants will wear miniature inertial measurement units (IMUs) (23 x 32.5 x 7.6 mm) for seven days to capture their daily life mobility. The IMUs will be affixed to the body using medical adhesive tapes (e.g., lower back) and/or straps (e.g., on the ankle). The sensors include an onboard data logger that is suitable for collecting longitudinal movement data. The feasibility of collecting such data has already been demonstrated through the UK Biobank study (<https://www.ukbiobank.ac.uk/>), which included nearly 100,000 participants, and in clinical populations such as Parkinson's disease in the ongoing MobiliseD project (Micó-Amigo et al., 2023).

The collected IMU movement data will undergo post-processing to extract walking bouts and their respective lengths. Following the definition by Micó-Amigo et al. (2023), a walking bout is defined as 'a walking sequence containing at least two consecutive strides of both feet.' To evaluate daily life gait quantity, parameters such as steps/strides per day and the number of turns will be derived. Quality of gait will be assessed based on the extracted walking bouts, including the calculation of parameters such as stride length, stride variability, and gait symmetry.

Sample size was calculated based on the desired precision of the foot placement control estimate. SD and error margin are estimated from pilot data on foot placement control in PD:

$$N = \left( \frac{z * sd}{error} \right)^2$$

$$N = \left( \frac{1.96 * 0.25}{0.07} \right)^2 = 49$$

**Population:** 126 PD patients

#### Associations between daily life gait and gait performance

##### **Dependent variables:**

*secondary clinical outcomes (T1-To):*

- $\Delta$  steps per day
- $\Delta$  uninterrupted walk durations
- $\Delta$  stride time variability
- $\Delta$  symmetry

##### **Independent variables:**

*primary clinical outcomes (T1-To):*

- $\Delta$  preferred gait speed (20 m walk test)
- $\Delta$  stride length (at preferred speed)

*secondary clinical outcomes (T1-To):*

- $\Delta$  stride length variability (at preferred speed)
- $\Delta$  stride time (at preferred speed)
- $\Delta$  stride time variability (at preferred speed)
- $\Delta$  step width (at preferred speed)
- $\Delta$  step width variability (at preferred speed)

*feedback control variables (T1-To):*

- $\Delta R^2$  (feedback model relating foot placement to centre of mass movement)
- $\Delta$  RMS error (feedback model relating foot placement to centre of mass movement)
- $\Delta$  Position gain (feedback model relating foot placement to centre of mass movement)
- $\Delta$  Velocity gain (feedback model relating foot placement to centre of mass movement)

*gait efficacy (T1-To):*

- $\Delta$  mGES

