**Dependent variables:**

*primary clinical outcomes (T1-To / T2-To):*

- $\Delta$  preferred gait speed (20 m walk test)
- $\Delta$  stride length (at preferred speed and at 1.4 km/h)

*secondary clinical outcomes (T1-To / T2-To):*

- $\Delta$  stride length variability (at preferred speed and at 1.4 km/h)

- $\Delta$  stride time (at preferred speed and at 1.4 km/h)
- $\Delta$  stride time variability (at preferred speed and at 1.4 km/h)
- $\Delta$  step width (at preferred speed and at 1.4 km/h)
- $\Delta$  step width variability (at preferred speed and at 1.4 km/h)

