##### **Analysis technique:**

We will correlate changes in daily-life outcomes with changes in lab-based gait performance outcomes. Multilevel models will be used to account for data collected at different sites. We will perform mediation analysis to assess the role of gait efficacy. In addition, in an exploratory analysis we will use machine learning to generate prediction models of the dependent variables

listed here based on the independent variables listed and patient characteristics such as age, disease duration, and disease severity.

x. Factors influencing individual treatment success (3c)

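### Analysis 3c takes the treadmill stride and step-width predictors at preferred speed only and commits to no model with change in speed, so these associations cannot separate better gait pattern from walking faster (minor).

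*Protocol*

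**What the plan says.** Section 6.ix lists the independent variables for 3c as changes from T0 to T1. The first is change in "preferred gait speed (20 m walk test", that is, overground speed. Six treadmill measures follow, all tied to preferred speed: "stride length (at preferred speed", "stride length variability (at preferred speed", stride time, "stride time variability (at preferred speed", step width, and "step width variability (at preferred speed". None is listed at 1.4 km/h.

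The other analyses of these measures (6.iv to 6.viii: 1a, 1b, 2a, 3a, 3b) take them at both speeds. In 3b, for instance, the list includes "step width variability (at preferred speed and at 1.4 km/h".

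The 3c technique reads: "We will correlate changes in daily-life outcomes with changes in lab-based gait performance outcomes". Multilevel models handle site, mediation analysis is planned for gait efficacy, and exploratory prediction models draw on the listed variables. No adjustment for change in speed is stated.

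The foot-placement predictors appear in 3c as "feedback control variables (T1-To", with no speed label. Elsewhere they are at 1.4 km/h.

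Section 4.iii makes change in gait speed the primary endpoint and puts daily-life gait on an exploratory level.

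**The concern.** Objectives 2 and 3 (section 4.ii) ask how far laboratory gains carry over to daily life, and by what mechanism. A participant whose preferred speed rises may show a different stride length, stride time, step width or variability at that speed simply because the speed differs. If people who gain speed also walk more at home, each such measure will correlate with daily-life change even if it has no role of its own.

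The fixed-speed condition exists to hold speed constant. Only 3c leaves it out, and no reason is given. What is at stake is the reading of the 3c associations: gait pattern and speed stay mixed for six of the listed predictors.

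**Working it through.** **1. The plan's own figure.** Section 6.ix gives a precision-based sample size: (1.96 × 0.25 / 0.07)² = 7² = 49. It reproduces. It concerns the foot-placement estimate and does not bear on the choice of predictors.

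**2. Predictor lists side by side.**

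| Analysis | Stride and step-width measures |
|---|---|
| 1a, 1b, 2a, 3a, 3b | preferred speed and 1.4 km/h |
| 3c | preferred speed only |

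**3. Which measures carry speed by construction.** On a treadmill, mean stride length = belt speed × mean stride time. If belt speed changes, at least one of the two must change. For step width and the variability measures, dependence on speed is an assumption.

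**4. Illustrative size.** The protocol gives no correlations, so these are assumed:
- r₁ = correlation of change in speed with daily-life change = 0.3
- r₂ = correlation of change in speed with change in the gait measure = 0.3 to 0.5

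If the measure has no effect of its own, the induced correlation is r = r₁ × r₂, so 0.3 × 0.3 = 0.09 and 0.3 × 0.5 = 0.15. Sample sizes are N = 126 (section 6.ix) and 126 × 0.8 = 100.8, about 101 (20% drop-out, section 6.i). The chance of p < 0.05, two-sided, by Fisher z is Φ(δ − 1.96) + Φ(−δ − 1.96), with δ = atanh(r) × √(N − 3):

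| r | N = 101 | N = 126 |
|---|---|---|
| 0.09 | δ = 0.893, 14.5% | δ = 1.001, 17.0% |
| 0.15 | δ = 1.496, 32.2% | δ = 1.676, 38.8% |

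A simulation (4,000 runs per setting) gave 14.2% and 16.5% for r₂ = 0.3, and 32.2% and 38.2% for r₂ = 0.5. With r₁ from 0.2 to 0.5 and r₂ from 0.3 to 0.7, the range was 8% to 95% at N = 101 and 11% to 99% at N = 126.

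With change in speed in the model the rate was 4% to 5%. It was 5% to 6% for a measure drawn as unrelated to change in speed, which stands for the ideal fixed-speed case and holds by construction. The adjusted result also assumes that the relevant speed change is measured without error, whereas 20-m overground speed is only a proxy for treadmill speed.

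**5. How far 1.4 km/h is from usual walking.** 1.4 / 3.6 = 0.39 m/s, and 0.39 / 1.26 = 31% of the baseline speed in section 6.i.

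**6. Whether the fixed-speed change can be computed.** At T0 (section 5.vii.A) the 5-minute walk is at 1.4 km/h, then repeated at preferred speed. The T1 and T2 text (5.ix.A and 5.xi.A) first puts the 5-minute walk at preferred speed, then discusses the fixed 1.4 km/h, then says the walk is repeated at preferred speed. Analyses 2a, 3a and 3b need fixed-speed data after baseline, so the intention can be inferred, but the text is not clear.

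**The case against.** Several counter-arguments stand.

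- **Speed change is already a predictor.** A joint model would reduce the problem. The technique neither commits to one nor excludes one, and a statistical analysis plan not at hand may settle it. What remains is that the enumerated list omits the fixed-speed versions.
- **Preferred speed suits the question.** Daily-life walking is self-paced, and 1.4 km/h is slow. The preferred-speed predictors should stay.
- **Adjusting for speed can over-adjust.** Section 3 treats slow walking as a consequence of short strides, so conditioning stride length on speed removes part of the pathway. Given belt speed, stride length and stride time also carry nearly the same information. A blanket belt-speed covariate would be wrong, and nowhere does the protocol say that belt speed is recorded for analysis.
- **The target is only association.** The 15% to 39% is not a type I error rate for the stated analysis. It is the chance that a speed-driven association is read as an effect of gait pattern.

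A reader might infer that 3c will credit the wrong mechanism. The documents do not support that. The hypothesised mechanism is foot-placement coordination (section 5.ii, WP2). Those variables are among the 3c predictors and are at 1.4 km/h in every other analysis.

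A reader might also take the planned gains as the size of the bias: up to 0.10 m/s, and up to 0.08 m/s more, on 1.26 m/s (0.10 / 1.26 = 7.9%; 0.18 / 1.26 = 14.3%). These are upper figures for overground speed, and a mean rise common to everyone induces no correlation between change scores. Only between-person variation in speed change does.

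**Conclusion.** The point holds, as a minor one. For the six stride and step-width measures, 3c as written cannot distinguish an association of gait pattern with daily-life change from an effect of walking faster. That follows from the predictor list and the stated technique. The size does not: the figure of about 15% to 39% rests wholly on the assumed correlations, and the wider grid of 8% to 99% shows how little the protocol fixes it. The analysis is exploratory and associational. The primary endpoint and the randomised comparison are unaffected.

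**What to change.** In section 6.ix:

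1. Keep the preferred-speed predictors. Add alongside them the 1.4 km/h versions of stride length variability, stride time variability, step width and step width variability, already planned for 3b.
2. For those four measures at preferred speed, also report the association with the already listed change in 20-m gait speed in the same model.
3. Do not adjust stride length or stride time in this way. Describe their associations as including speed.

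In sections 5.ix.A and 5.xi.A, reconcile the description of the treadmill walks so that the fixed-speed walk at T1 and T2 is clear.

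The cost is wording and a few more exploratory models, using measures that 3b already requires. Because 1.4 km/h is slow relative to daily-life walking, the fixed-speed results supplement the preferred-speed results and do not replace them.

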##### **Analysis technique:**

We will correlate changes in daily-life outcomes with changes in lab-based gait performance outcomes. Multilevel models will be used to account for data collected at different sites. We will perform mediation analysis to assess the role of gait efficacy. In addition, in an exploratory analysis we will use machine learning to generate prediction models of the dependent variables

listed here based on the independent variables listed and patient characteristics such as age, disease duration, and disease severity.

x. Factors influencing individual treatment success (3c)

**Aims:**

This WP will focus on the qualitative (interview) data combined with quantitative data from previous analyses to determine:

- (i) why treadmill/enhanced training may improve lab-based gait outcomes in some but not other people; and
- (ii) why lab-based gait outcomes may transfer to improved daily-life gait in some but not other people;

We aim to provide a holistic understanding of the mechanisms underlying the transfer of changes in clinic-based gait outcomes to changes in real-world mobility outcomes, their retention and the barriers and enablers to wide spread treatment uptake and long-term acceptance.

**Population:** 126 PD patients

**Analysis technique:**

We will focus on understanding the differences between individuals who do and do not improve on the lab-based tests, and individuals who do and do not improve in their daily-life related outcomes. We will use machine learning to investigate, for example, the relative importance to successful intervention of: (i) baseline demographics, education, sex, age, and socioeconomic status; (ii) experiences and preferences of persons with PD; (iii) clinical gait and balance outcomes; (iv) changes in lab-based gait and mechanistic outcomes; and (v) social and psychological factors for individual outcomes in daily-life, such as mobility, quality of life. This is critical towards developing more personalized and long-term effective therapies that improve walking and prevent falls in people with PD.

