### ii. Objectives

Thus, the **objectives** of our StepuP project are:

1. To understand the kinematic and neural mechanisms that underlie improvements in gait due to treadmill training with and without mechanically and VR-triggered gait adaptations in people with PD;
2. To assess to what extent improvements in gait due to treadmill training, as measured in the lab, transfer to improvements in daily life mobility;
3. To understand the mechanisms that underpin transfer from improvements in gait to improvements of mobility in daily life in people with PD;
4. To understand for whom treadmill training improves lab-based gait characteristics and for whom it does not, and understand for whom treadmill training improves mobility in daily life and for whom it does not.

Attaining these objectives will provide a better understanding of the successes and failures of treadmill training to improve gait stability and prevent falls in people with PD at an individual level, which in the medium term will allow targeted delivery of such interventions and in the long term will allow personalization of such interventions to improve outcomes for all.

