### ii. Analysis plans and datasets

The statistical analysis of the outcomes will comprise the definition of analysis sets and statistical analysis (including prioritization of outcomes).

---

 <https://app.sampsize.org.uk>

The main aim is to determine the mechanisms underlying effects on gait performance in clinical tests and in daily-life of SDTT. This entails an analysis of pooled data (excluding the healthy control participants). Nested within this design, several randomized comparisons will be made to assess the added value of the SDTT+ components over SDTT. Initially a placebo comparison was planned but given the proven effect of SDTT this was deemed unethical. To interpret the any effects changes in the absence of a placebo control group it is first of all important to determine the minimal meaningful change for the outcome parameters. In addition, a comparison between participants with and without PD will be done to support interpretation of effects in the PD group. These analysis to this end are described as analysis 1a and 1b. Subsequently the nested randomized comparisons are described as levels 2a to 2c. Finally, the analysis to test hypothesis on the causality of changes in gait performance will be described as analyses 3a and 3b.

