### iv. Analysis of reliability (1a)

#### **Population:**

From the populations measured in Sydney 21 participants chosen at random will participate in an additional measurement set 14 days prior to start of the intervention (T-1). This sample is kept small for pragmatic reasons. First, it is not feasible to apply this additional measurement in all participants at all centers. Second, in case a systematic effect of repeated testing is found, this may need to be statistically corrected for or the sub-sample of individual participants with this additional baseline may need to be omitted in the pooled analyses (3a and 3b).

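### Objective 4 is addressed by comparing patients who do and do not improve on observed change, with every patient trained, so individual training response cannot be told apart from retest error, practice, fluctuation or regression to the mean.

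*Protocol*

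**What the plan says.** Objective 4 (Protocol section 4.ii) is "To understand for whom treadmill training improves lab-based gait characteristics and for whom it does not", with a parallel aim for mobility in daily life. The same section links the objectives to targeted and, later, personalised delivery of training.

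Section 6.x, Factors influencing individual treatment success (3c), names the population as "126 PD patients". Its analysis focuses on "understanding the differences between individuals who do and do not improve on the lab-based tests", with a matching comparison for daily-life outcomes. Machine learning is then to rank example groups of predictors, among them "changes in lab-based gait and mechanistic outcomes". The section does not mention a contrast between randomised arms.

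Section 5.viii gives SDTT to every patient in both arms. Section 6.ii explains the lack of an untreated group: "Initially a placebo comparison was planned but given the proven effect of SDTT this was deemed unethical". For that reason, it continues, "it is first of all important to determine the minimal meaningful change for the outcome parameters".

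Section 6.iv (1a) supplies the material for this: in Sydney, "21 participants chosen at random will participate in an additional measurement set 14 days prior to start of the intervention (T-1"). It uses the resulting limits of agreement to judge effects in analyses 2a-2c, and raises correction for a retest effect, or omission of the twice-tested patients, for 3a and 3b. It does not mention 3c.

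**The concern.** A patient's change from before to after training is not that patient's response to training. It also contains test-retest error, practice with the test, day-to-day fluctuation and regression to the mean. With no untrained group, these parts cannot be separated for an individual, and patients will fall into improvers and non-improvers even if all benefit equally.

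Analysis 3c depends most on single-patient change, yet it is the one to which the repeat-baseline safeguard is not assigned. The result could be that patients are described as not benefiting, and characteristics as explaining why, when the data cannot tell this from noise. The objective is meant to inform who is offered training.

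**Working it through.** **The plan's own figure.** The protocol gives no figure for 3c, so the only planning inputs are those of section 6.i: difference 0.08 m/s, SD 0.08 m/s, alpha 0.05, power 0.80. Taken as two-sided, a t-based two-sample calculation at a standardised difference of 0.08/0.08 = 1 gives 16.71, so 17 per group, as stated. The protocol does not say whether 0.08 is the SD of change; that is assumed below, with a range of 0.06 to 0.15.

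**Apparent non-improvers when everyone has the same true benefit m.** Counting any change above zero as improvement, the share not improving is Φ(−m/SD).

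| True change m (m/s) | SD 0.08 | Of 126 | Range for SD 0.06 to 0.15 |
|---|---|---|---|
| 0 | Φ(0) = 50% | 63 | 63 |
| 0.05 | Φ(−0.625) = 27% | 34 | 25 to 47 |
| 0.10 | Φ(−1.25) = 10.6% | 13 | 6 to 32 |

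The 0.10 is borrowed from section 6.i, where it is an upper figure for SDTT against overground walking, not a pre-post change. The 0 and 0.05 are assumed values.

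**Would a stricter threshold solve it?** Take 1.96 SD as the cutoff, as limits of agreement would suggest.
- With no true change, 2.5% are classed as improved, about 3 of 126.
- With a common true change of 0.10, the share is 1 − Φ(1.96 − 1.25) = 24%. The other 76% would not count as improved, although all benefit equally.

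A threshold limits false claims of improvement but does not identify non-responders.

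**Regression to the mean, if baseline gait is among the predictors.** With a constant effect and equal variances at both visits, the correlation of baseline with change is −√((1 − r)/2), where r is test-retest reliability (assumed).
- r = 0.95: −0.16
- r = 0.90: −0.22
- r = 0.80: −0.32

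In a simulation of 1,000,000 patients with r = 0.80, SD of change 0.08 and a common true change of 0.05, 84% of the slowest baseline third improved against 61% of the fastest third, with no difference in true response.

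**Precision of the limits from the repeat baseline.** The standard error of one limit is SD × √(1/n + 1.96²/(2(n − 1))). For n = 21 it is 0.38 SD, or 0.03 m/s at SD 0.08.

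**Interval of the repeat baseline.** Section 6.iv places it 14 days before training starts; section 5.iv describes a 6-week extension of the pre-training phase. These must be reconciled before the data can serve as a no-training reference.

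**The case against.** Several arguments on the other side have force.

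- **The protocol recognises the problem.** It plans a repeat baseline because there is no untreated group. This stands, but the safeguard is assigned to other analyses, and it addresses measurement error, not regression to the mean. The analysis labels in section 6 are loose (3c heads two sections, and 2b and 2c have none of their own), so the omission may be an oversight; it still needs correcting.
- **Detail may be left to a statistical analysis plan.** This stands for the cutoff, the algorithm and the covariates. Section 6.x also reads as exploratory and gives its predictors as examples. But the protocol itself sets the pooled population and the comparison of improvers with non-improvers.
- **There may be more than one measurement before and after.** Gait speed is taken at T0, T1 and T2 (section 5.xii), and the 20-m walk is repeated during training (section 5.viii). Section 6.x does not say which values it uses. Averaging would reduce error but would not remove practice or supply an untrained contrast.
- **The illustrated share may be small.** If the SDTT+ arm gained 0.18 m/s (0.10 + 0.08), its share would be Φ(−2.25) = 1.2%. With 63 patients per arm, 63 × 0.106 + 63 × 0.012 is about 7 of 126. This is fair: the size depends on the true change, which is unknown, and 0.18 adds two upper figures.
- **The randomised contrast answers a different question.** Interactions with arm show for whom the added perturbations help, not for whom SDTT itself works. This stands and limits what they can be used for.

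**Conclusion.** The point holds in this form: as section 6.x is written, observed improvement cannot be told apart from retest error, practice, fluctuation or regression to the mean, so it cannot show who responds to training. With an SD of change of 0.08 m/s and the same benefit in everyone, about 11% would appear not to improve at a true change of 0.10 m/s and about 27% at 0.05 m/s. Both the SD and the true changes are assumptions.

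Three stronger readings are tempting but not supported.
- **That noise would be reported as responders and non-responders.** Some of the variation may be real; the design cannot say how much.
- **That the protocol enters baseline gait as a predictor, so that regression to the mean will certainly appear.** The word baseline is attached to the demographic group, not to the clinical gait and balance group.
- **That the prediction is circular because change in lab gait predicts itself.** The machine-learning sentence ends with daily-life outcomes, for which change in lab gait is a legitimate predictor. The overlap arises only where success is defined as lab-based improvement.

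**What to change.** 1. In 3c, replace the improver/non-improver split with continuous follow-up values adjusted for baseline. Report the results as exploratory predictors of change, not of treatment response.
2. Add exploratory arm-by-baseline-characteristic interactions from the randomised SDTT+ versus SDTT comparison. State that they show only for whom the added perturbations help, and that they will be imprecise with 126 patients.
3. Where lab-based improvement is the outcome, do not use change in lab gait as a predictor. It may stay as a predictor of daily-life outcomes.
4. Extend the test-retest limits to 3c for describing individual patients, once the 14-day and 6-week statements are reconciled. Note that limits from 21 patients are imprecise and do not remove regression to the mean.

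The cost is analysis and wording, on data already planned. The price is a more modest conclusion for objective 4: for SDTT itself, the trial can describe who changed, not who responded.
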